### Feasibility and acceptability of the training

Feasibility of the training will be assessed by considering (i) the number of patients who complete the 2-week training and (ii) the number of sessions completed per patient. These values, expressed as percentage and mean percentage will be extrapolated at T1. Higher values will indicate higher feasibility. Lastly, the acceptability will be assessed by asking the child/adolescent and his/her parents’ subjective evaluation of training accessibility and efficacy. The questionnaires will be adapted from the study of Butti et al. (48). Questions like “I find it difficult to motivate my child for doing the training”/“I find it difficult to start the training”; or “I would suggest this training to other people I know”/“I think other people I know would enjoy doing this training” will be rated from 1 (completely disagree) to 5 (completely agree). Response will be reversed in the negative items, so that higher scores will suggest more positive evaluation/higher acceptability.

## Interventional methods

### Transcutaneous nerve vagus stimulation

Transcutaneous nerve vagus stimulation allows the non-invasive stimulation of the Vagus Nerve by delivering electrical pulses to the sensory afferent fibers of the auricular, thick-myelinated, branch of the vagus nerve in the outer ear. tVNS will be performed by using a CE-marked tVNS device tVNS®E (tVNS, technologies GMBH, Erlangen, Germany). It consists in a programmable stimulation unit connected to two titan ear electrodes that are mounted on a gel frame, allowing to generate and transfer electric impulses from the stimulation unit to the surface of the skin, where the electrodes are applied. The active tVNS will be applied through an active electrode placed on the cymba conchae (innervated by the auricular branch of the vagus nerve), while the sham stimulation will be administered by positioning the active electrode in correspondence of the earlobe, which is free of cutaneous vagus innervation (see Figure 3). Applying active stimulation in both the experimental and control groups, but at differently innervated positions of the ear skin, will allow for sham-control stimulation without hindering blindness to stimulation condition. To avoid cardiac effects, the electrodes will be applied to the left ear. The stimulation intensity will be set based on the perceptual threshold of the participants, corresponding to the perceived intensity and below the perception of pain, in order to make the stimulation tolerable. The device’s stimulation intensity ranges from 0.1 to 5 mA for individuals aged 3 years and older. However, in the present project the stimulation intensity will be constrained to range from a minimum of 0.5 mA to a maximum of 3 mA, falling within the range used in previous tVNS studies with pediatric populations (49). This will limit the risk of any major side effects (e.g., skin irritation) despite any sensorial deficits that may blur participants’ sensitivity to stimulation. In any case, the stimulation will be interrupted if participants would not tolerate the stimulation at the lowest predefined intensity. The intensity of the stimulation will be gradually increased to reach the intensity of stimulation with a ramping-up phase of 30 s. In both active and sham conditions, on (28 s) and off (32 s) periods of stimulation will be alternated, with pulses delivered every 200–300 μs at a frequency of 25 Hz. These are the most common parameters applied in tVNS studies, as outlined in a recent review on parameters settings for neurological and psychiatric disorders (50), and they are the default parameters of the CE-marked tVNS device used in this study. The tVNS, sham or active, will be applied for the first 75 min of the training, every day of the treatment. Given the duty cycle of alternating on and off periods, participants will receive 35 min of stimulation over a 75-min period in each session. Discontinuation to interventions will be contemplated in case of serious adverse effects, withdrawal of consent or significant changes in the participant’s health status, such as the development of any contraindication to the stimulation, that make continuing the intervention unsafe or inappropriate.

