## Design

This clinical trial represents one of the two Randomized Clinical Trials (RCT) of the project “Bottom-up and tOp-down neuromOdulation of motor plaSTicity in cerebral palsy” (BOOST; FRRB 3438840). The study is a randomized, double-blind, sham-controlled pre-post-test study involving 44 children and adolescents with CP. Patients will be treated in pairs, with a matching of motor deficit severity, IQ, or age, by meeting at least two out of these three criteria. Motor severity will be defined on the basis of the Manual Ability Classification System (MACS) level and classified as low to middle (I-II level) or as middle to high (II-III). With respect to age, two group levels will be identified for children (from 6 to 11 years old patients) and adolescents (12–17 years old patients). With respect to IQ, low IQ value (from 50 to 70) and high IQ value (> 71) will be distinguished. Each pair will be randomly assigned to the active or to the sham tVNS group. The randomization will be stratified based on IQ, MACS level, or age. As for the matching within each pair, at least two out of these three criteria must be encountered.

Both groups will undergo a bimanual training in an ecological and highly motivating environment while carrying out bimanual tasks, including recreational play activities during the application of the tVNS protocol. During the training, starting from a set of proposals the choice of the type of activities to be practiced in each session will be left to patients, boosting the motivational aspect of the training. This will also ensure an individualized and goal-directed approach. The therapists will monitor and modify the activities within each pair to ensure that the intervention maintains the quality of the individualized intervention. The positions performed during bimanual tasks and the activities of daily living will be designed to systematically engage postural control of the trunk and lower limbs according to Habit-ILE protocol. The training will be carried out by a therapist with expertise in maintaining the 1:2 ratios. Training activities will be carried out for 5 consecutive days for 3 h/day for 2 weeks (30 h of intervention overall). Children and adolescents will be assessed 1 or 2 days before the start of the treatment (T0), 1 or 2 days after the end of the treatment (T1), and at a follow-up after 3 months (T2).

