**Figure 1 fig1:**
[figure not shown]
Flow chart of patient’s inclusion and experimental procedures. ^*^The PedsQL and VABS-II will be administered only at T0 and T2, while all other measures will be administered at all timepoints.

Each pair of patients will be randomly assigned to one of two groups (active vs. sham group) with an allocation ratio 1:1, through a computer-generated blocked randomization procedure conducted by independent personnel not directly involved in performing the intensive training. The patients and their parents, the personnel responsible for conducting the bimanual training and analyzing clinical data will be kept blind to the group allocation. Instead, the coordinator of the study and the personnel administering the tVNS will be “not blind.” With respect to the clinical assessment, the staff administering and scoring the scales will be blinded to group allocation. Questionnaire scores and neuropsychological tests will not contain personal information about the patients, who will be identified by an alphanumeric code. All records that contain names or other personal identifiers, such as informed consent forms, will be stored separately from study records identified by code number. In order to uphold the overall quality and credibility of the clinical trial, instances of code breaks should be limited to exceptional circumstances, where knowledge of the actual treatment is deemed absolutely necessary for the ongoing management of the patient. The intensive treatment will take place at the Scientific Institute, IRCCS E. Medea in Bosisio Parini (Lecco, Italy; study sponsor), Fondazione Mondino IRCCS in Pavia (Italy), and ASST Ospedali Civili in Brescia (Italy). The SPIRIT checklist used for protocol reporting can found in the Supplementary material.

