
**Figure 3 fig3:**
[figure not shown]
Schematic depiction of the electrode placements in the active and sham stimulation condition. To deliver active stimulation, the two titanium electrodes are placed on the outer auditory canal of the left ear. For sham stimulation, the two titanium electrodes are positioned on the center of the left earlobe.

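### The stated blinding of the training therapists is not supported: the electrode site on the left ear differs by arm for 12.5 of the 30 training hours, and no concealment is described

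*Protocol article*

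**What the plan says.** **The blinding claim.** The Design section states: "The study is a randomized, double-blind, sham-controlled pre-post-test study". The allocation paragraph after Figure 1 assigns the roles. Patients and parents are to be blind, and "the personnel responsible for conducting the bimanual training and analyzing clinical data will be kept blind to the group allocation". For the assessments, "the staff administering and scoring the scales will be blinded to group allocation". On the other side, "the coordinator of the study and the personnel administering the tVNS will be" unblinded. The training therapist is therefore on the blinded list and is not among the exceptions.

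**The electrode sites.** The section on transcutaneous vagus nerve stimulation says: "The active tVNS will be applied through an active electrode placed on the cymba conchae". For sham, the same section moves the electrode to the earlobe. The Figure 3 legend agrees on the sham site: "For sham stimulation, the two titanium electrodes are positioned on the center of the left earlobe". For the active site the legend names the outer auditory canal. Both arms use the left ear.

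**The timing and the setting.** Stimulation, active or sham, runs in the first 75 min of the training on every treatment day. On staffing, the Design section says: "The training will be carried out by a therapist with expertise in maintaining the 1:2 ratios".

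**The reason given for blinding.** Real current is delivered in both groups, and doing so "at differently innervated positions of the ear skin, will allow for sham-control stimulation without hindering blindness to stimulation condition".

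**The concern.** A different-site sham needs two separate protections. The participant must not be able to tell the arms apart by sensation. Blinded people near the participant must not be able to tell them apart by sight. Delivering current in both arms addresses the first. It does nothing for the second, because the change of site that is meant to make the sham inactive is also the visible marker of the arm.

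The therapist's blinding matters because the training is not a fixed dose. Children choose the type of activity from a set of proposals, but the therapist monitors and modifies the activities (Design), and the HABIT-ILE section describes tasks made progressively harder, ongoing feedback and support of motivation. A therapist who knows the arm could, without intending it, push harder or encourage more in one arm. That would be a real difference in training, so blinded scoring of the Assisting Hand Assessment and the Box and Block Test would record it faithfully and could not remove it. The Discussion says that the comparison isolates the specific modulatory effect of the stimulation. That requires the training to be delivered alike in both arms.

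**Working it through.** The point rests on setting statements side by side. The only arithmetic is the exposure time.

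**1. Who is said to be blind?** The training personnel are (allocation paragraph, Design).

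**2. What differs between arms on the outside of the body?** The electrode position on the left ear: cymba conchae (text) or outer auditory canal (Figure 3 legend) for active, earlobe for sham. The text and the legend do not name the same active place, but either one differs from the earlobe.

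**3. For how long is the electrode in place during training?**
- Per day: 75 min of a 3 h (180 min) session, 75/180 = 42%.
- Over the course: 75 min × 10 sessions = 750 min = 12.5 h.
- Total training: 3 h × 10 = 30 h, and 12.5/30 = 42%.

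This counts the off periods of the duty cycle, because the electrode stays on the ear. It assumes that all 10 sessions are completed.

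**4. Who is present?** A therapist working with two children. Both members of a pair share an arm, so a therapist sees only one site per session. One site is enough for someone who knows which is active, and a therapist who treats several pairs may see both.

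**5. Does the stated reason cover this person?** No. It rests on stimulation being felt in both arms.

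**6. Is there another safeguard in the text?** No cover, headband, screen or fitting out of sight is described. The safety section has the skin at the electrode site inspected before and after each application but does not say by whom.

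**Illustration of what a bias could do.** The article gives no figure for an expectation effect, so the sizes below are assumptions. Take no true effect of stimulation, n = 22 per arm treated as independent, and a bias of d standard deviations of the change score. For a two-sided 5% t-test on 2 × 22 − 2 = 42 df, the noncentrality is d × √(22/2):

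| Assumed d | Noncentrality | Chance of a significant result |
|---|---|---|
| 0 | 0 | 5.0% |
| 0.1 | 0.33 | 6.2% |
| 0.2 | 0.66 | 9.9% |
| 0.3 | 0.99 | 16.3% |
| 0.4 | 1.33 | 25.4% |

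The group-by-time interaction test on 2 and 84 df, under compound symmetry, gives 6.1%, 9.5%, 15.7% and 25.1% for d = 0.1 to 0.4 if the bias persists in full at T2. At d = 0.4 it gives 19.7% if the bias halves by T2. These figures show sensitivity only. They do not estimate the bias in this trial.

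**The case against.** **Visibility is inferred.** No sentence says that the ear is uncovered, and Figure 3 is not available. This is a journal article, and the means of hiding an electrode is detail that a fuller protocol could hold. The article also gives stimulation and training to different people. This stands as a limit: the article does not prove that therapists will see the site. It does not remove the point, because the article makes a positive claim about therapists and the only reason it offers does not reach them.

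**The sentence on ear sites may be meant only for sensation.** Read that way it is sound. The therapist claim in the allocation paragraph is then left with no support.

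**A reader might infer that the double-blind design fails as a whole.** The documents do not support that. Raters and analysts are separately stated to be blind, assessments take place outside the training sessions, the visuomotor task is computer-based, and nothing shows that these safeguards break down.

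**A reader might also infer that children and parents are unblinded, and that the child-rated occupational performance scores and the parent-rated hand-use questionnaire are therefore biased.** That is speculative. Pair-mates share one arm and see no contrast, no sentence places parents in the sessions, and seeing one site is not the same as knowing which is active. Their blinding is less certain, not shown to fail.

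**Therapist discretion is limited,** since the children choose the type of activity. Modification, grading and feedback remain with the therapist.

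**Conclusion.** The stated blinding of the training personnel is not supported by the design as written. The electrode position on the outer ear differs by arm and is in place for 12.5 of 30 training hours beside a therapist who is listed as blind. The stated reason concerns the participant's sensation only, and no concealment is described. The consequence is possible performance bias through how the training is adapted and encouraged. Its size is unknown, and the percentages in the table hold only under the assumed expectation effects and with children treated as independent although pairs are randomised.

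The conclusion rests on one inference, that an electrode at these sites can be seen by someone working with the child. If the ear is already covered in practice, one added sentence settles the point. It should be corrected, but it does not invalidate the trial.

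**What to change.** Amend the allocation paragraph in Design and the section on transcutaneous vagus nerve stimulation to state that:

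- the unblinded stimulation personnel fit and remove the electrode, and inspect the skin, out of the therapist's sight;
- the same opaque ear cover or headband is worn over the left ear in both arms for the whole stimulation period.

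If this is not practicable, take the training personnel off the blinded list and describe the trial as participant- and assessor-blind. In either case, reconcile the active site named in the text with the one in the Figure 3 legend.

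Asking child, parent and therapist at T1 to guess the arm, and reporting the guesses by arm, would be useful but is optional.

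The cost is a few reusable covers and a short procedural amendment. Unblinded personnel are already in the plan, so fitting and removal need no new role. The article does not say whether they stay for the full 75 min, so that should be settled. The downside is small: slight discomfort, and the cover must be lifted for checks. Restating the blinding costs only wording, but it leaves possible performance bias as a limitation to report.

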
**Figure 3 fig3:**
[figure not shown]
Schematic depiction of the electrode placements in the active and sham stimulation condition. To deliver active stimulation, the two titanium electrodes are placed on the outer auditory canal of the left ear. For sham stimulation, the two titanium electrodes are positioned on the center of the left earlobe.

### HABIT-ILE protocol

Hand-Arm Bimanual Intensive Therapy Including Lower Extremities (12) is an intensive rehabilitation strategy of bimanual training that continuously incorporates postural control and lower extremity function (13). It is based on the assumption that lower extremity, postural function and interlimb coordination may benefit from being directly targeted in combination with the upper extremity. The Habit-ILE is based on motor learning and problem-solving, through the identification of problems, definition of tasks and progressive strategies to reach the objectives. It involves highly structured practice during which tasks requiring simultaneous control and coordination of upper and lower extremities are performed. In the Habit-ILE protocol, basic principles for inducing plastic change in the motor cortex are exploited, by means of repeated practice and gradual increase of task demand in a motivated and rewarding setting. In this vein, intervention will be based on child’s motor abilities (determined at baseline), age, interests and self-identified functional goals with parents’ advice (e.g., drinking by him/herself without spilling, tie the shoes, taking off/on a t-shirt, etc., as emerged also from the assessment with the COPM scale). According to the Habit-ILE protocol, tasks/activities will be made incrementally more challenging and the environment will be adapted to allow success of the child but still challenging the motor demands. Each child will start at a level, which he/she can easily achieve. At the lowest level, the more affected Upper Extremity will be used as a passive stabilizer, with progressive encouragement toward more complex (active) use. The tasks that will be performed include: (I) incremented table-top fine motor activities, performed in a seated position; (II) activities of daily living when sitting/standing/walking; and (III) gross motor play and physical activities. The involvement of the Lower Extremities in the different activities will also be progressed from sitting stable activities through an unsupported sitting and sitting on an unstable support, such as on a roller or a ball or a balance board, to dynamic activities, e.g., crawling, walking, running or jumping. More skilled/challenging Upper Extremity activities will be introduced in stable sitting, and then the Upper Extremity Activities that have been mastered will be carried out in more challenging conditions involving also Lower Extremities. During practice, ongoing feedback about performance will be provided. Activities will be presented as games and the environment will be arranged in such a way that children perceive it as fun (i.e., learning magical tricks, playing sports activities etc.), with the intent to increase motivation and compliance not only at the individual level, but also between the two participants. In this regard, the action of the therapists will focus on a few main aspects: fostering child-environment interaction (not only spatial environment, but also relational environment); promoting and supporting attention and motivation in the creation of the action plan so that both purely motor and sensory skills, as well as cognitive and emotional-relational skills, will be involved in the construction of the rehabilitation project. The involvement of experienced and *ad-hoc*-trained physical and occupational therapists is expected to ensure the consistent application of treatment methods, thereby enhancing adherence and maintaining fidelity to the intervention protocol. Importantly, the use of goal-directed activities chosen by the pair of children is expected to reduce frustration and provide the necessary motivation for repetitive bimanual activities. Participation in other clinical trials in the period spanning from 2 months before the beginning of this RCT until the follow up evaluation will be an exclusion criterion, in order to avoid interference with the study protocol and results. Standard care will be allowed.

## Sample size calculation

Using the GPower 3 software (51) with the “as in SPSS option” we estimated that, with a mixed design comprising the between group factor (active group vs. sham group) and the within variable (Pre T0-, post T1-, follow-up T2, numerator DF = 2), a sample of 22 subjects per group allows detecting, with a power of 0.80 and an alpha level set at 0.05, a between group difference between active and sham tVNS combined motor training of moderate to large effect size [f (U) = 0.35], which is expected to lead to a clinically-relevant improvement in motor activity and dexterity.

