## Statistical analysis

Statistical analyses will be performed using STATISTICA 8.0 (StatSoftInc, Tulsa, Oklahoma). Demographic and clinical variables of the two groups of patients will be inspected through descriptive statistics. Independent sample *t*-test (two-tailed) and χ^2^ will be used to assess the differences between the experimental and control training groups at baseline for continuous and categorical variables, respectively, thus allowing us to verify successful randomization. The outcome measure data will undergo a normal distribution assessment using Kolmogorov–Smirnov tests. If the data adheres to a normal distribution, repeated measures ANOVAs will be employed to analyze differences between treatment group (active vs. sham) and across timepoints (T0-T1-T2) on the primary and secondary outcomes. Duncan *post hoc* tests will be performed to follow-up significant interactions and correct for multiple pair-wise comparisons. Conversely, for data not following a normal distribution, the Kruskal-Wallis H test or Friedman test will be applied. The exploratory analysis will center on investigating sex and age differences in treatment response, considering both primary and secondary outcomes. Furthermore, in light of findings on hemisphere-specific tVNS effects cortical excitability (20) and electrophysiological readiness potentials (52), we will conduct a sensitivity analysis. This analysis will examine potential differences in tVNS effects when administered ipsilateral or contralateral to the side of the most affected limb. Statistical significance will be denoted by *p* < 0.05. As to what concerns missing data, a modified intention-to-treat analysis approach will be adopted, including in the analyses all the participants who had completed the pre- and post-treatment evaluation sessions, even if they had not completed all the training sessions. No imputation of missing data, however, will be used considering the limited sample size and observation points.

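### Pairs are randomised and trained together, but the sample size and the ANOVA count 44 independent children; if changes within a pair correlate, the planned test exceeds 5% and a valid 5% test has less than 0.80 power

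*Protocol article*

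**What the plan says.** **Unit of randomisation.** The Design section of the protocol article says "Each pair will be randomly assigned to the active or to the sham tVNS group". The text after Figure 1 repeats it: "Each pair of patients will be randomly assigned to one of two groups (active vs. sham group) with an allocation ratio 1:1". The Discussion says the same again. Both members of a pair therefore go to the same arm.

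**How pairs are formed and treated.** The Design section says "Patients will be treated in pairs, with a matching of motor deficit severity, IQ, or age", with at least two of the three criteria met, and has one therapist work with two children. The HABIT-ILE protocol section has the two children choose their goal-directed activities together.

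**Sample size.** The total is 44 children. The Sample size calculation section says "a sample of 22 subjects per group allows detecting, with a power of 0.80 and an alpha level set at 0.05", an effect "of moderate to large effect size [f (U) = 0.35" in brackets. It uses the G*Power option that follows SPSS, with a between-group factor and "the within variable (Pre T0-, post T1-, follow-up T2, numerator DF = 2". Pairs are not mentioned.

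**Analysis.** In the Statistical analysis section, "repeated measures ANOVAs will be employed to analyze differences between treatment group (active vs. sham) and across timepoints (T0-T1-T2" in brackets. Kruskal-Wallis or Friedman tests replace the ANOVA when data are not normal. The model has group and time, but no pair. No ICC, design effect or pair-level analysis appears anywhere in the article.

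**The concern.** The unit that is randomised differs from the unit that is counted. Allocation acts on 22 pairs, while the power calculation and the ANOVA act on 44 children.

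The group-by-time test compares changes over the visits. Two children who share a therapist, sessions and activities for 30 hours may well change alike. If they do, the difference between arm means varies more than the child-level error term suggests. The F ratio is then too large on average when there is no treatment effect. A test that uses the correct error term has fewer degrees of freedom and a smaller noncentrality.

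This test carries the trial's main comparison, active against sham tVNS, on every primary outcome. An inflated false positive rate could produce a claim of benefit that the data do not support. A power figure that assumes independence would mislead readers about what a null result means.

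**Working it through.** **Inputs from the protocol article.** N = 44 children; k = 2 groups; m = 3 visits; numerator df = 2; f(U) = 0.35; alpha = 0.05; stated power 0.80; pairs allocated 1:1, hence 22 pairs and about 11 per arm.

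**Assumed input.** The ICC of change within a pair is not given. The range 0 to 0.5 is an assumption. Sphericity and complete pairs are also assumed.

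**Step 1: reproduce the stated figure.** Under the SPSS convention:

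- lambda = f(U)² × (N − k) × (m − 1) = 0.1225 × 42 × 2 = 10.29
- df = 2 and (N − k)(m − 1) = 42 × 2 = 84
- power from the noncentral F distribution = 0.812

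With N = 42 the same formula gives 0.791. So 44 is the smallest even N that reaches 0.80 when children are independent, and the calculation contains no allowance for pairs.

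**Step 2: power of a valid pair-level test.** With two children per pair, the design effect is 1 + (2 − 1) × ICC = 1 + ICC. The noncentrality becomes 10.29/(1 + ICC), and the error df become (22 − 2) × 2 = 40. For ICC 0.2, lambda = 10.29/1.2 = 8.575, and power with df 2 and 40 is 0.715.

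**Step 3: true level of the planned ANOVA.** This was simulated with 11 pairs per arm, two interaction contrasts with the same ICC, no treatment effect, and 40,000 trials per ICC. Each trial was tested at child level with df 2 and 84.

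| ICC of change (assumed) | Effective N = 44/(1 + ICC) | Type I error, planned ANOVA | Power, valid pair-level test |
|---|---|---|---|
| 0 | 44.0 | 0.051 | 0.796 |
| 0.05 | 41.9 | 0.058 | 0.775 |
| 0.1 | 40.0 | 0.065 | 0.754 |
| 0.2 | 36.7 | 0.081 | 0.715 |
| 0.3 | 33.8 | 0.101 | 0.678 |
| 0.5 | 29.3 | 0.142 | 0.611 |

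The pair-level test stayed at 0.049 to 0.052 throughout. Repeat simulations differ by up to about half a percentage point.

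**Step 4: detectable effect.** Solving for f(U) so that 84 × f(U)²/(1 + ICC) gives 80% power with df 2 and 40 yields about 0.35 (ICC 0), 0.39 (ICC 0.2) and 0.43 (ICC 0.5).

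**The case against.** **The ICC is unknown and may be small.** This stands. At ICC 0 the planned test holds its level and the pair-level power is 0.796, in effect the stated figure. At ICC 0.05 the damage is slight. Nothing in the article supports a value as high as 0.5. A reader might infer that the type I error certainly exceeds 5%, but the documents do not support that, because it depends on a positive ICC.

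**Matching is weak evidence for a positive ICC.** This also stands in part. Matching on severity, IQ or age makes levels alike. The group-by-time test depends on change, so matching counts only as far as these factors predict response. The article also individualises training to each child's abilities and goals, and sets stimulation intensity per participant. These features lower the expected ICC without removing it: the shared therapist, sessions and activities remain, and they act on change directly.

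**The planned ANOVA would still reject about 80% of the time.** Correct. In simulation under f(U) = 0.35 it rejected in 0.79 to 0.81 of trials at every ICC. A reader might infer that the planned test itself loses power. It does not, because its true level has risen. What falls is the power of a test that really holds 5%. Part of that fall (0.812 to 0.796) comes only from the error df dropping from 84 to 40.

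**An analysis plan that is not shown could add a pair term.** It could repair the analysis. It would not repair the sample size statement, which gives 0.80 power for independent children.

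**Perhaps one child of each pair goes to each arm.** The Design section and the Discussion assign the pair as a whole to one group, so this reading does not fit.

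**Conclusion.** The mismatch of units is explicit, and nothing else in the article resolves it. Its consequences are conditional on the ICC. For any positive ICC of change, the planned group-by-time test exceeds 5% and a valid 5% test falls below the stated 0.80. Shared training makes a positive ICC the reasonable expectation, but its size is unknown.

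Over the assumed ICC values 0, 0.05, 0.1, 0.2, 0.3 and 0.5, the type I error is about 5%, 6%, 6.5%, 8%, 10% and 14%, and the valid power is about 0.80, 0.77, 0.75, 0.71, 0.68 and 0.61. Confidence is high in the mismatch and in the direction of both effects, and moderate in their size. Because this concerns the main comparison and the remedy is cheap, it should be corrected before the analysis.

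**What to change.** 1. State that the pair is the unit of randomisation: 22 pairs, about 11 per arm. Keep 44 children.
2. Replace the ANOVA by a linear mixed model with group, visit and their interaction, and random effects for pair, pair-by-visit and child within pair. Use small-sample degrees of freedom based on 22 pairs, for example Kenward-Roger. The model also copes with pairs left with one child, which can happen because children without the post-treatment assessment are excluded. Testing pair means with error df 40 is an alternative when all pairs are complete.
3. In the non-parametric branch, use pair-level summaries or a test that permutes whole pairs between arms.
4. Restate the power of the valid test, or the effect detectable with 80% power, under an explicit ICC assumption. For example: power about 0.71 at f(U) = 0.35, or detectable f(U) about 0.39, if the ICC is 0.2.

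The cost is a less favourable power figure and a little more analysis work. No extra patients are needed to make the test valid. If the sponsor wants 80% power at f(U) = 0.35 instead, the same pair-level formula, with equal whole pairs per arm, gives 52 children at ICC 0.1, 56 at 0.2 and 68 at 0.5.
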